## Abstract

**Background:**

In the intensive care unit (ICU), critical illness delirium occurs in the context of multiple comorbidities, multi-organ failure, and invasive management techniques, such as mechanical ventilation, sedation, and lack of sleep. Delirium is characterized by an acute confusional state defined by fluctuating mental status, inattention, and either disorganized thinking or an altered level of consciousness. The long-term cognitive and psychosocial function of patients that experience delirium in the ICU is of crucial interest because preliminary data suggest a strong association between ICU-related delirium and long-term cognitive impairment.

**Objective:**

The aim of this study is to explore the relationship between delirium in the ICU and adverse outcomes by following mechanically ventilated patients for one year following their discharge from the ICU and collecting data on their long-term cognition and psychosocial function.

**Methods:**

This study will be conducted by enrolling patients in two tertiary ICUs in Australia. We aim to recruit 200 patients who have been mechanically ventilated for more than 24 hours. Data will be collected at the following three time points: (1) at discharge where they will be administered the Mini-Mental State Examination (MMSE); (2) at 6 months after discharge from the ICU discharge where the Impact of Events Scale Revised (IES-R) and the Telephone Inventory for Cognitive Status (TICS) tests will be administered; and (3) at 12 months after discharge from the ICU where the patients will be administered the TICS and IES-R tests, as well as the Informant Questionnaire for Cognitive Decline in the Elderly (IQCODE). The IQCODE will be administered to their “person responsible” or the significant other of the patient.

**Results:**

Long-term cognition and psychosocial function will be the primary outcome of this study. Mortality will also be investigated as a secondary outcome. Active enrollment will take place until the end of September 2016 and data collection will conclude at the end of September 2017. The analysis and results are expected to be available by March 2018.

**Conclusion:**

Delirium during mechanical ventilation has been linked to longer ICU and hospital stays, higher financial burdens, increased risks of long-term cognitive impairment (ie, dementia), poor functional outcomes and quality of life, and decreased survival. However, delirium during mechanical ventilation in the ICU is not well understood. This study will advance our knowledge of the comprehensive, long-term effects of delirium on cognitive and psychosocial function.

**Trial Registration:**

Australian New Zealand Clinical Trials Registry (ANZCTR): ACTRN12616001116415; https://www.anzctr.org.au/Trial/Registration/TrialReview.aspx?id=371216 (Archived by WebCite at http://www.webcitation.org/ 6nfDkGTcW)

## Introduction

Delirium is a disturbance of consciousness, developed over a short period of time, where inattention is accompanied by a change in cognition and/or perceptual disturbance [1]. Delirium occurs in a variety of health care settings [2] and affects between 15% to 20% of general hospital patients [3,4], including as many as 80% of critically ill, intensive care unit (ICU) patients receiving mechanical ventilation [5].

In the ICU, delirium is associated with critical illness itself, particularly with multiple comorbidities and multi-organ failure, as well as management-related factors such as mechanical ventilation, sedation, and lack of sleep [2,6,7]. Delirium is also associated with adverse outcomes including death and long-term cognitive impairments [7-9], and potentially traumatic stress symptomatology. Several studies suggest delirium-related risks are cumulative and may foster the development of cognitive dysfunction, poorer functional status, and impair quality of life [7-23]. Despite literature reports of a reduced quality of life for survivors of critical illness and delirium in the ICU, the long-term follow-up of cognitive and psychosocial function still remains relatively unexplored. This study will address this by following up with patients for one year after discharge from the ICU. We will employ a set of tests that complement each other [24] in order to create a comprehensive view of a patient's cognition and psychosocial well-being at 12 months after leaving the ICU. These tests assess cognition and evidence of post-traumatic stress disorder (PTSD) [25], while also using each patients “person responsible” to assess their relative's and/or friend’s psychosocial function at 12 months after their discharge from the ICU in comparison to their pre-ICU psychosocial abilities. This study is expected to provide novel insight into the cognitive and psychosocial impact of ICU mechanical ventilation-related delirium and to assist in improving the care of critically ill intensive care patients by highlighting the importance of the need to monitor for the development of delirium.

## Methods

We are conducting a prospective case-control study in two ICUs in Australia: the Canberra Hospital in the Australian Capital Territory and the Prince of Wales Hospital in Sydney, New South Wales. The study was approved by the ACT Health Human Research Ethics Committee (ETH.6.12.130) and the Southern Health Human Research Committee (12/242 (HREC/I2/POWH/460). Since eligible participants are not able to give informed consent on enrolment due to their health status (ICU treatment), their substitute decision maker or “person responsible” will be identified. This person is approached to provisionally consent to participation on behalf of the patient. The “person responsible” is given a full explanation of the study and is provided with the Cognitive and Psychosocial Assessment (CAPA) study information sheet. They are then asked to consent to participate in the study on behalf of themselves and the patient. If the patient is not sedated or delirious, the study is explained to them; however, the “person responsible” is still required to complete and sign the consent form on behalf of themselves and the patient whilst the patient is ventilated. Further, consent from the “person responsible” authorizes their later involved in the assessment of patients’ overall function at the 12-month follow-up.

Despite being recruited to the study through their “person responsible,” the patients receive no other intervention other than standard protocol care during their ICU stay. The standard care in both recruiting sites involves administering the following during mechanical ventilation: (1) the Richmond Agitation and Sedation Score (RASS) [26,27], and (2) the Confusion Assessment Method for the ICU (CAM-ICU) [28].

After being recruited to the study, the patients have their sedation level assessed by the RASS [26,27] every 4 hours. The RASS is a scale that indicates the patient’s level of sedation and ranges from +4 to –5. A RASS score of 0 represents a patient who is alert and calm, while positive scores indicate different levels of agitation from restless (+1) to combative (+4). Negative scores indicate different levels of drowsiness from drowsy (–1) to unarousable (–5).

Patients with a RASS score between –2 and +3 will be administered the CAM-ICU [28]. The CAM-ICU is an adaptation of the Confusion Assessment Method and is widely used for diagnosing delirium with yes and no questions for use with non-speaking, mechanically ventilated patients in the ICU. The study participants are not exposed to any additional testing during their time in the ICU.

Patients assessed as suffering delirium via the CAM-ICU at any time are allocated into the delirium positive study group, while delirium-negative patients are re-tested on a daily basis during the time they remain mechanically ventilated. Those patients who never test positive for delirium are allocated to the delirium-negative group (Figure 1).

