### Participants

Patients participating in this study are critically ill, mechanically ventilated, and may require immediate administration of sedative medications by infusion. As a consequence of the immediacy of the situation and the urgent need for sedation, we obtain provisional consent from the patient’s “person responsible” prior to enrolling patients in the study. Adult patients greater than 18 years of age are approached for recruitment after being mechanically ventilated for more than 24 hours. The exclusion criteria are (1) suspected acute primary brain lesion; (2) end stage liver failure or acute hepatic failure; (3) culturally and linguistically diverse (CALD) background—literature suggests that in times of crisis people automatically revert to their own language and our psychosocial questionnaires are not specifically designed for CALD [29,30]; (4) death is deemed imminent and inevitable; (5) patient is a nursing home resident and/or physical/cognitive decline is evident [31,32]; and (6) the Acute Physiology and Chronic Evaluation (APACHE II) [33] classification indicates underlying terminal illness.

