## Results

The primary outcome of this study is the assessment of long-term cognition and psychosocial function. Patient mortality will be the study's secondary outcome. Active enrollment will take place until the end of September 2016 and data collection will conclude at the end of September 2017. The analysis and results are expected to be available by March 2018.

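### As worded, the delirium-negative group needs no negative CAM-ICU result, so a ventilated patient never in the testable RASS range would join it untested

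*Protocol article*

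**What the plan says.** Four statements in the Methods section of the protocol article fix the exposure.

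- Who is tested: "Patients with a RASS score between –2 and +3 will be administered the CAM-ICU". The same section describes RASS as running from +4 down to –5, so levels –3 to –5 (and +4) lie outside the testing range.
- Who is exposed: "Patients assessed as suffering delirium via the CAM-ICU at any time are allocated into the delirium positive study group".
- When testing continues: "delirium-negative patients are re-tested on a daily basis during the time they remain mechanically ventilated".
- Who is unexposed: "Those patients who never test positive for delirium are allocated to the delirium-negative group". This sentence refers the reader to Figure 1, which is not reproduced in the text we have.

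The Participants section describes patients ventilated for more than 24 hours who "may require immediate administration of sedative medications by infusion". None of its six exclusion criteria removes a patient who cannot be tested. Textbox 1 (Measures) lists RASS and CAM-ICU as daily items and, at ICU discharge, records delirium status in two categories only, with survival status alongside.

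On outcomes, the Results section states: "Patient mortality will be the study's secondary outcome". Cognition is measured first by the MMSE at ICU discharge, after the patient has confirmed consent, and then by the TICS at 6 and 12 months.

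**The concern.** A patient can fail to test positive in two ways: by being tested with negative results, or by never being tested. The written rule does not separate them. Someone at RASS –3 or below throughout ventilation has no CAM-ICU result, so by the letter of the rule belongs in the comparison group.

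Such patients would not be a random subset. They are untested because they are deeply sedated or unarousable, and the Introduction itself links delirium to sedation and multi-organ failure. Group membership is the study's only exposure, so every between-group comparison would inherit the error. The regression adjustment foreseen under Statistical Analysis cannot repair a mislabelled exposure. If the negative group is small, a few misplaced patients weigh heavily, and the Introduction cites delirium in as many as 80% of ventilated ICU patients.

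**Working it through.** **1. Following the rule for an untestable patient.** The CAM-ICU requires RASS –2 to +3. A patient outside that range at every assessment while ventilated has no CAM-ICU result and hence no positive result, so is allocated to delirium-negative. No stated exclusion, minimum number of tests or third category interrupts this chain.

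**2. Which outcomes can be affected.**
- *Cognition.* Only patients who survive, confirm consent at ICU discharge and are then assessed contribute scores. A patient who dies untested contributes none. The only route is a survivor who had no testable assessment before extubation.
- *Mortality.* A patient who dies deeply sedated may never have been tested. This matters only if ICU deaths enter the comparison. Textbox 1 records survival at ICU discharge, but patient consent is sought at that same point, and the article does not say whether ICU deaths are analysed.

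**3. The plan's sample size.** Inputs from the Sample Size section: difference 2 MMSE points, alpha .05 (two-sided assumed), power 80%, 81 per group. No SD is stated, so 81 can only be back-solved.

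Normal approximation: SD = 2 × √(81/2) / (1.960 + 0.842) = 12.73 / 2.802 ≈ 4.54. Putting 80 in place of 81 gives 4.51, so 81 corresponds to an SD between 4.51 and 4.54. With the t test the SD is about 4.5 (n = 80.4 at SD 4.50, 80.8 at 4.51). SD 4.5 is used below.

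**4. Dilution of the cognitive difference (illustration).** Assume a share *c* of the negative group has the same mean outcome as the delirious group. The expected difference is then 2 × (1 – *c*). Two-sided t test, 81 per group, SD 4.5:

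| *c* (assumed) | Difference | Power |
|---|---|---|
| 0 | 2.0 | 80% |
| 5% | 1.9 | 76% |
| 10% | 1.8 | 72% |
| 20% | 1.6 | 61% |
| 30% | 1.4 | 50% |

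Using the normal approximation with SD 4.54 changes these powers by no more than about half a percentage point.

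**5. How few patients would make up such a share (illustration).** Let a share *u* of the 200 enrolled be never testable, and let a proportion *p* of the testable be delirious. The untested share of the negative group is 200*u* / [200*u* + 200(1 – *u*)(1 – *p*)].

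| *u* (assumed) | Untested | Share if *p* = 50% | Share if *p* = 80% |
|---|---|---|---|
| 2% | 4 | 4/102 = 4% | 4/43.2 = 9% |
| 5% | 10 | 10/105 = 10% | 10/48 = 21% |
| 10% | 20 | 20/110 = 18% | 20/56 = 36% |

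These shares are at enrolment and include patients who later die. The share among survivors with cognitive scores would differ, so this table should not be read straight into the one in step 4.

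**6. Mortality (illustration, all risks assumed).** Take a risk of death of 15% if tested negative, 30% if positive and 60% if never tested. Risk in the negative group = 0.15(1 – *c*) + 0.60*c*. At *c* = 10% this is 19.5%, and the difference from the delirious group falls from 15 to 10.5 points. At *c* = 20% it is 24%, and the difference is 6 points.

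**The case against.** The strongest reply is that the authors meant tested patients. Only someone already tested can be re-tested, so in context never testing positive may describe repeated negative tests. RASS is scored every 4 hours, which gives many chances to find a testable state. The allocation sentence points to Figure 1, whose legend covers both RASS and CAM-ICU, and a not-testable branch could be drawn there. These points lower the certainty that anyone would be misplaced. They do not alter the written rule, which requires no valid negative test.

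Three stronger readings are tempting and are not supported.

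- *Patients who die before becoming assessable dilute the cognitive comparison.* They cannot, because they have no cognitive score. Most survivors probably pass through a testable level, so the cognitive effect may well be small.
- *Deaths in untested patients are loaded onto the negative group and may reverse the mortality association.* This requires ICU deaths to be analysed, which the article leaves open. Consent is confirmed at ICU discharge, follow-up runs from there, and patients whose death is imminent are excluded. In step 6, the sign would reverse only above *c* = (0.30 – 0.15)/(0.60 – 0.15) = one third, under invented risks.
- *Delirium arising after extubation is counted as negative, against the study's aim.* The abstract does say "The aim of this study is to explore the relationship between delirium in the ICU and adverse outcomes", but that sentence goes on to specify ventilated patients, and the hypothesis under Measures concerns delirium during mechanical ventilation. Methods also counts a positive result at any time, and Textbox 1 lists the CAM-ICU as daily without a ventilation limit. What remains is a difference in wording.

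**Conclusion.** The point holds as a defect in a stated definition. Applied literally, the rule classes a never-tested patient as delirium-negative, subject to what Figure 1 shows. The mortality comparison is the more exposed, if ICU deaths are included. The cognitive comparison is exposed only through survivors untested before extubation.

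The article does not show that any patient would be misclassified, and it gives no share of untestable patients. The bias is zero if everyone is tested at least once. The figures of 1.8 or 1.6 points and 72% or 61% power are hypothetical. They rest on assumed shares of 10% and 20%, on those patients having delirious-like outcomes, on a back-solved SD of about 4.5 and on 81 per group. They show that a modest share would matter, not that it will occur. This calls for a correction to the definition; it is not evidence that the comparisons are already biased.

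**What to change.** - Define delirium-negative as at least one valid CAM-ICU (RASS –2 to +3) during ventilation, with all valid results negative.
- Put patients with no valid CAM-ICU in a separate not-assessable category, outside the two-group comparison. Report their number, characteristics and outcomes descriptively, and add them back in a sensitivity analysis.
- Add the third category to the status recorded at ICU discharge, and check that Figure 1 agrees.
- Align the abstract's reference to delirium in the ICU with the hypothesis, which concerns delirium during mechanical ventilation.

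The cost is one classification sentence and small wording edits. RASS and CAM-ICU are already recorded daily, so no new data are needed. The downside is that a few patients leave the main comparison.

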**Figure 1 figure1:**
[figure not shown]
a. CALD Culturally and Linguistically Diverse Background; b. APACHE II Acute Physiology and Chronic Health Enquiry II; c. RASS Richmond Agitation Sedation Scale; d. CAM-ICU Confusion Assessment Method for the Intensive Care Unit; e. MMSE Mini Mental State Examination.

### Participants

Patients participating in this study are critically ill, mechanically ventilated, and may require immediate administration of sedative medications by infusion. As a consequence of the immediacy of the situation and the urgent need for sedation, we obtain provisional consent from the patient’s “person responsible” prior to enrolling patients in the study. Adult patients greater than 18 years of age are approached for recruitment after being mechanically ventilated for more than 24 hours. The exclusion criteria are (1) suspected acute primary brain lesion; (2) end stage liver failure or acute hepatic failure; (3) culturally and linguistically diverse (CALD) background—literature suggests that in times of crisis people automatically revert to their own language and our psychosocial questionnaires are not specifically designed for CALD [29,30]; (4) death is deemed imminent and inevitable; (5) patient is a nursing home resident and/or physical/cognitive decline is evident [31,32]; and (6) the Acute Physiology and Chronic Evaluation (APACHE II) [33] classification indicates underlying terminal illness.

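### The period in which delirium counts is not anchored in time, so delirium that clears before consent can be classed as delirium-negative

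*Protocol article*

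**What the plan says.** Recruitment opens only once a patient has been ventilated for some time: "Adult patients greater than 18 years of age are approached for recruitment after being mechanically ventilated for more than 24 hours" (Participants). The article states no upper limit. Enrolment also waits for a proxy: "we obtain provisional consent from the patient’s “person responsible” prior to enrolling patients in the study" (Participants).

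The Methods section places the study's assessments after that point: "After being recruited to the study, the patients have their sedation level assessed by the RASS [26,27] every 4 hours". A RASS score in the stated range leads to the CAM-ICU, and the CAM-ICU decides the group: "Patients assessed as suffering delirium via the CAM-ICU at any time are allocated into the delirium positive study group". Negative patients are re-tested daily while ventilated, and "Those patients who never test positive for delirium are allocated to the delirium-negative group".

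The same section says that both instruments are routine: "The standard care in both recruiting sites involves administering the following during mechanical ventilation", followed by RASS and CAM-ICU. It adds that "The study participants are not exposed to any additional testing during their time in the ICU".

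Textbox 1 (Measures) lists the date and time of first intubation among the enrolment items, but no earlier CAM-ICU result. CAM-ICU appears under the daily items, and delirium status is recorded at ICU discharge.

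**The concern.** Delirium status is the exposure in this observational comparison, so every between-group result depends on how it is assigned. Recruitment starts more than 24 hours into ventilation and depends on reaching a person responsible, so every patient has a ventilated period before enrolment. Delirium can occur and resolve in that period.

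Read in the order written, the assigning sequence starts at recruitment. Consider a patient who is CAM-ICU positive on day 2, clear by day 4, consented on day 5 and not positive again. Under that reading the patient never tests positive within the study sequence and joins the comparison group. Exposed patients in the unexposed group pull the two group means together and weaken any true association with later cognition, psychosocial function or mortality.

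**Working it through.** **Does the text settle the window?**

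| Element | Points to counting from recruitment | Points to counting all ventilated time |
|---|---|---|
| Start of RASS (Methods) | Described as following recruitment | – |
| CAM-ICU (Methods) | Follows from that RASS sequence | Standard care during ventilation; no added testing |
| Group rules (Methods) | Placed inside the post-recruitment sequence | Worded without any time limit |
| Textbox 1 (Measures) | No earlier CAM-ICU among enrolment items | Daily items not restricted to days after enrolment; status recorded at ICU discharge |

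Both readings are available, and no sentence shown chooses between them. Under the first, the example patient is delirium-negative; under the second, delirium-positive.

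**The plan's own figure.** Sample Size gives a 2-point MMSE difference, alpha 0.05, 80% power and 81 per group. No SD is given, so 81 cannot be checked independently. Solving backwards with the normal approximation, two-sided (sidedness is assumed):

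SD = 2 × √(81/2) / (1.960 + 0.842) = 12.73 / 2.802 ≈ 4.54.

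With SD 4.54 the formula returns 81 per group and power 80.1%, so the stated figures are consistent with that SD.

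**Illustration of dilution.** Let m be the share of the delirium-negative group that was delirious only before consent. Assume that these patients carry the full deficit. The expected difference becomes 2(1 − m), and

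power = Φ(2.80 × (1 − m) − 1.96).

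| m (assumed) | Expected difference | Power at 81 per group | n per group for 80% |
|---|---|---|---|
| 0% | 2.0 | 80% | 81 |
| 5% | 1.9 | 76% | 90 |
| 10% | 1.8 | 71% | 100 |
| 20% | 1.6 | 61% | 127 |
| 30% | 1.4 | 50% | 166 |

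Allowing for the extra variance of a mixed negative group changes little: 71%, 60% and 49% at m = 10%, 20% and 30%.

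**How m could arise.** Let p be the proportion of enrolled patients with delirium, and f the fraction of those who were positive only before recruitment and were counted as negative. Then m = pf / (pf + 1 − p).

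- p = 80% (the upper figure in the Introduction for ventilated ICU patients), f = 5%: 0.04 / 0.24 ≈ 17%.
- p = 80%, f = 10%: 0.08 / 0.28 ≈ 29%.
- p = 50% (assumed), f = 10%: 0.05 / 0.55 ≈ 9%.

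The article gives neither f nor m. These lines show only that a modest f can produce values in the tabulated range when delirium is common.

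**The case against.** The strongest reply is that the text can be read the other way. CAM-ICU is routine during ventilation, the study adds no testing, and neither group rule is limited to the time after consent. On that reading the exposure data are the routine results, earlier positives count, and m from this mechanism is zero. The phrase about recruitment grammatically governs the 4-hourly RASS and does not define an exposure window. Figure 1, cited for group allocation, is not shown, and it or the full protocol may settle the matter. This stands to the extent that misclassification is possible under the text but not prescribed by it. A reader might infer that the article classes pre-consent delirium as negative; no sentence says so.

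The reply also limits the size of the effect. To be misclassified, a patient must be positive before consent, clear before consent, and stay negative on daily re-testing while ventilated. Such brief delirium may not carry the full deficit. The power figures are therefore illustrations.

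A reader might further infer that recruiters select patients by delirium status, because results exist before the approach and the consent procedure refers to it ("If the patient is not sedated or delirious, the study is explained to them"). The documents do not support that. The wording shows that status can be known at the approach, but the person responsible must sign for every ventilated patient, delirious or not, and nothing says that CAM-ICU results guide whom to approach. Nor does the missing upper limit on recruitment amount to a defect: a cut-off, a consecutive-approach rule and a screening log are details that an article commonly leaves to the full protocol, and a cut-off would lose patients.

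The reply does not remove the ambiguity. The group rule is written in this article, and two sites following it could place the same patient in opposite groups.

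**Conclusion.** The point holds as an ambiguity in the exposure definition. As written, delirium that cleared before consent can be classed as delirium-negative, which would bias the group contrasts towards no difference. The article neither states that this will happen nor rules it out.

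The size is unknown. Power of about 71%, 61% or 50% at m = 10%, 20% or 30% rests on an assumed m, a two-sided test, the SD implied by 81 per group, and the full 2-point deficit in misclassified patients. If earlier results are already meant to count, there is no loss from this source and one sentence of clarification is enough. The correction is worth making because it costs little and concerns the variable on which every comparison depends.

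**What to change.** State in the Methods section that the exposure window runs from first intubation to the end of mechanical ventilation. A patient with any positive routine-care CAM-ICU result in that window, including one charted before consent, is delirium-positive; a patient with none is delirium-negative. Add the CAM-ICU results from before enrolment to Textbox 1. If Figure 1 or the full protocol already says this, bring the article's wording into line with it.

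The cost is a small amount of chart abstraction. The date and time of first intubation are already collected, and standard care already produces the CAM-ICU results, so no patient needs a new test and the statement that there is no additional testing remains true.

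Optionally, record the time from intubation to consent and the CAM-ICU status at approach, so that the extent of pre-consent delirium can be described.
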